### Safety monitoring

The over-all rate of bleeding complications will be compared with historical data from the NORSTROKE Registry 2007–2011, the Pooled analysis of iv alteplase trials [57], SITS-MOST [60, 61], ECASS III [59] and series on thrombolysis in patients above 80 years of age [62]. The mortality rate at 7 days will be compared with historical data from NORSTROKE 2007–2011.

All Suspected Unexpected Serious Adverse Reactions (*SUSARs)* are reported to the Norwegian Medicines Agency. All serious adverse events (SAE), i.e., bleedings and deaths, are reported within 24 h to the Executive working group (EWG). The EWG routinely submits a safety report to the independent Data Safety Monitoring Committee (DSMC) after each 40 enrolled patients (20 per group). If the DSMC finds unacceptably increased sICH with CEST+ thrombolysis as compared with sham CEST+ thrombolysis, the study may be stopped for further analysis. If CEST+ tenecteplase shows a 2 % excess of sICH as compared with CEST+ alteplase, the tenecteplase tier may be stopped and the study may be continued with only alteplase patients. The same stopping rule is applied to CES vs. sham CES in patients not eligible for iv thrombolysis.

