**Methods/Design:**

Acute ischaemic stroke patients ≥18 years, with or without visible arterial occlusion on computed tomography angiography (CTA) and treatable ≤ 4½ hours after symptom onset, are included in NOR-SASS. NOR-SASS is superimposed on a separate trial randomising patients with acute ischemic stroke to either tenecteplase or alteplase (The Norwegian Tenecteplase Stroke Trial NOR-TEST). The NOR-SASS trial has two arms: 1) the thrombolysis-arms (NOR-SASS A and B) includes patients given intravenous thrombolysis (tenecteplase or alteplase), and 2) the no-thrombolysis-arm (NOR-SASS C) includes patients with contraindications to thrombolysis. First step randomisation of NOR-SASS A is embedded in NOR-TEST as a 1:1 randomisation to either tenecteplase or alteplase. Second step NOR-SASS randomisation is 1:1 to either contrast enhanced sonothrombolysis (CEST) or sham CEST. Randomisation in NOR-SASS B (routine alteplase group) is 1:1 to either CEST or sham CEST. Randomisation of NOR-SASS C is 1:1 to either contrast enhanced sonolysis (CES) or sham CES. Ultrasound is given for one hour using a 2-MHz pulsed-wave diagnostic ultrasound probe. Microbubble contrast (SonoVue®) is given as a continuous infusion for ~30 min. Recanalisation is assessed at 60 min after start of CEST/CES. Magnetic resonance imaging and angiography is performed after 24 h of stroke onset. Primary study endpoints are 1) major neurological improvement measured with NIHSS score at 24 h and 2) favourable functional outcome defined as mRS 0–1 at 90 days.

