### Patient inclusion and exclusion criteria

All acute ischaemic stroke patients ≥ 18 years admitted within 4½ hours of symptom onset may be included in the study. An intracranial arterial occlusion on pre-treatment computed tomography angiography (CTA) is not a prerequisite for inclusion since this study also includes sonothrombolysis/sonolysis of the peripheral vascular bed and central perforating arteries. Study participation is based on informed consent requirements as approved by the ethics committee. Exclusion criteria are listed in Table 1.

**Table 1 Tab1:** Inclusion and exclusion criteria

Inclusion criteria
•Patients >18 years with acute ischaemic stroke, with or without a visible arterial occlusion, and start of treatment within 4 ½ hours after stroke onset.
General exclusion criteria
•Patients with premorbid modified Rankin Scale (mRS) score ≥3
•Patients for whom a complete NIH Stroke Score cannot be obtained
•Hemiplegic migraine with no arterial occlusion on baseline CT
•Seizure at stroke onset and no visible occlusion on baseline CT
•Intracranial haemorrhage on baseline CT
•Clinical presentation suggesting subarachnoid haemorrhage even if baseline CT is normal
•Large areas of hypodense ischaemic changes on baseline CT
Patients with primary endovascular treatment
•Pregnancy or breast feeding, pericarditis, sepsis, any other serious medical illness likely to interact with treatment, confounding pre-existent neurological or psychiatric disease, unlikely to complete follow-up, any investigational drug <14 days
Specific sonothrombolysis/sonolysis exclusion criteria
•Known hypersensitivity or allergy to SonoVue®
•Recent or unstable coronary ischemia or resting angina <7 days
•Acute cardiac insufficiency, cardiac insufficiency class III/IV; serious cardiac arrhythmias
•Any right-left-shunt, severe pulmonary hypertension (PAP >90 mmHg) Moderate to severe chronic obstructive pulmonary disease (chronic obstructive pulmonary disease (COPD), baseline O2 saturation <80 %)
•Acute respiratory distress syndrome (ARDS)

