### Assessment methods

Table 2 neurological deficit is documented with National Institutes of Health Stroke Scale (NIHSS). Function is documented with mRS and Barthel Index (BI). On admission, native computed tomography (CT) with CTA is performed for all patients within the therapeutic time window. Early CT ischaemic signs are semi-quantitatively assessed using the ASPECTS scoring system [49]. Intracranial middle cerebral artery (MCA) occlusions are trichotomised in none, distal (MCA_2_), or proximal (MCA_1_) occlusion. Other occlusions are defined as appropriate. Intracranial artery stenosis are described as minor (≤50 %), moderate (51-70 %) and severe (71-99 %) diameter reduction or occlusion. Magnetic resonance imaging and angiography (MRI/MRA) or CT/CTA is performed after 22–36 h to verify the infarct, assess intracranial recanalisation and to detect haemorrhagic transformation. Radiological assessment is performed by investigators blinded to the treatment given. Duplex ultrasound examinations are carried out the day after admission. Carotid stenosis grading is based on flow velocities calculated with a modified NASCET formula or with the internal-common carotid ratio (IC-CC ratio).

**Table 2 Tab2:** Assessment of patients with acute ischaemic stroke admitted ≤4½ hours

Procedure ↓	Timepoint→	Baseline	1-2 h	+24 h (22-36 h)	+48 h (42–54 h)	Day 7 or earlier discharge	Day 90
NIHSS score		X	X	X	X	X	(X)
CT / CTA (MRI / MRA)		X		X			
ECG		X					
Duplex ultrasound of the neck				X			
Transcranial duplex ultrasound		X	X	(X)		(X)	
Modified Rankin Scale (mRS)		X				X	X
Barthel Index (BI)						X	(X)
Check Recurrent stroke / TIA							X
Check Acute coronary heart disease							X

*(X)* optional

The amount of ultrasound delivery to the vasculature cannot be assessed in NOR-SASS. As a surrogate marker for attenuation through the skull, bone window thickness is measured by a physician blinded to clinical information, except for the window of insonation.

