### Safety outcome

Patients are monitored in the stroke unit (or intensive care unit (ICU) if appropriate) with NIHSS scoring at close intervals for 24–36 h. Safety is determined by the incidence of haemorrhagic transformation within 24-h of treatment on MRI (or CT when MRI is not possible) by a neurologist and/or neuroradiologist blinded to all clinical data. Classification of haemorrhagic transformation is left to the discretion of the local investigators. In case of disagreement, the scans are assessed by the Data Safety Monitoring Committee.

Haemorrhagic transformation (ECASS criteria) are categorised as *haemorrhagic infarction* 1 (HI1 = small petechiae along the margins of the infarct); *haemorrhagic infarction* 2 (HI2 = confluent petechiae within the infarcted area but no space-occupying effect); parenchymal haemorrhage 1 (*PH1* = blood clots in 30 % or less of the infarcted area with some slight space-occupying effect); p*arenchymal haemorrhage 2 (PH2* = blood clots in more than 30 % of the infarcted area with substantial space-occupying effect); and *Remote parenchymal haemorrhage (rPH =* bleeding outside the infracted area).

Symptomatic cerebral haemorrhage (sICH) is defined as local or remote parenchymal haemorrhage type 2 on the 22–36 h post-treatment imaging scan, combined with a neurological deterioration of 4 points or more on the NIHSS from baseline or from the lowest NIHSS value between baseline and 24 h, or leading to death *(SITS-MOST criteria)* [56]. In order to facilitate comparison with published studies, sICH is also assessed according to 1) NINDS /Cochrane criteria [57] as any haemorrhage plus any neurological deterioration [NIHSS score ≥1] or that leads to death within 7 days; 2) ECASS II criteria [58] as blood at any site in the brain on the CT scan, clinical deterioration or adverse events indicating clinical worsening (drowsiness, increase of hemiparesis) or causing an increase in the NIHSS score of 4 or more points; and 3) ECASS III criteria [59] as any apparently extravascular blood in the brain or within the cranium associated with clinical deterioration (defined by an increase in the NIHSS score of 4 or more points) or death, and that is identified as the predominant cause of the neurological deterioration.

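### The protocol article defines serious adverse events as bleedings and deaths, so other serious non-fatal events have no stated prompt route to the safety committee; as a minor point, the haemorrhagic-transformation window does not match its scan

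*Protocol article*

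**What the plan says.** All references are to the protocol article.

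**SAE reporting.** Safety monitoring says: "All serious adverse events (SAE), i.e., bleedings and deaths, are reported within 24 h to the Executive working group (EWG". The same section has this group send a safety report to the DSMC after each 40 enrolled patients. The sentence just before it requires all SUSARs to go to the national medicines agency.

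**Risks the protocol links to the intervention.** Table 1 has a separate block of exclusions specific to sonothrombolysis and sonolysis. It opens with "Known hypersensitivity or allergy to SonoVue" and goes on to recent or unstable coronary ischaemia, cardiac insufficiency, serious arrhythmias, severe pulmonary hypertension, obstructive lung disease and acute respiratory distress syndrome.

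**Other safety provisions.** Statistical analysis says that SAEs and AEs will be analysed, without detail. Table 2 checks recurrent stroke or TIA and acute coronary disease at day 90. Long-term follow-up registers vascular events and other complications at 3 months.

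**Timing of haemorrhagic transformation.** Safety outcome says: "Safety is determined by the incidence of haemorrhagic transformation within 24-h of treatment on MRI". Assessment methods has the imaging "performed after 22–36 h to verify the infarct, assess intracranial recanalisation and to detect haemorrhagic transformation", and Table 2 labels that visit as +24 h with a 22–36 h window. The abstract says: "Magnetic resonance imaging and angiography is performed after 24 h of stroke onset". Study endpoints gives 24–36 h for late recanalisation and lesion volume and no time for haemorrhagic transformation. Symptomatic cerebral haemorrhage (sICH) is "defined as local or remote parenchymal haemorrhage type 2 on the 22–36 h post-treatment imaging scan", together with clinical deterioration or death.

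**The concern.** An SAE is normally defined by its seriousness, not by its type. Here the definition is by type, and the two types named are the classic risks of thrombolysis. The experimental treatment also includes a contrast infusion, and the protocol itself keeps out patients whose allergic, cardiac or respiratory state makes that infusion hazardous. If a site follows the sentence as written, a serious but survived reaction of one of those kinds triggers no 24-h notice to the working group.

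This matters most in NOR-SASS C. No thrombolytic is given there, so the tested treatment is ultrasound plus contrast alone, and the Hypothesis section claims that it is safe. The DSMC is the body that reviews safety while the trial runs, and its reports come from the group whose expedited input is limited to bleedings and deaths.

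The second, smaller issue is that the outcome by which the article says safety is determined has a time limit that does not fit the scan meant to measure it.

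**Working it through.** The plan gives no figure to reproduce on this point. The first part is a comparison of texts; the second needs one division.

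**Part 1. Stated routes for each kind of event**

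| Event | 24-h notice to the working group | Other stated provision |
|---|---|---|
| Bleeding | Yes | Haemorrhage endpoints; sICH in the stopping rules |
| Death | Yes | Secondary endpoint; death registry |
| Serious, survived contrast reaction | None stated | AE analysis; SUSAR if it qualifies |
| Serious, survived cardiac event | None stated | AE analysis; day-90 check of acute coronary disease; SUSAR if it qualifies |
| Serious, survived respiratory event | None stated | AE analysis; complications at 3 months; SUSAR if it qualifies |
| Non-fatal recurrent ischaemic stroke | None stated | AE analysis; day-90 check |

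Three things follow.

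1. The last four rows have no stated 24-h route to the group that writes the DSMC report. The day-90 checks come months after a one-hour treatment and do not replace it.
2. The SUSAR rule and the SAE definition do not fit together. By the article's own list of abbreviations a SUSAR is a serious reaction, and nothing in the term confines it to bleeding or death. One sentence therefore assumes a class of serious events that the next sentence defines away.
3. The SUSAR rule does not fill the gap. It covers only reactions that are suspected and unexpected, and the stated recipient is the medicines agency. A reaction already anticipated in the exclusion list may be judged expected.

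**Part 2. The haemorrhagic-transformation window**

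Inputs: scan window 22–36 h (Assessment methods, Table 2); limit of 24 h after treatment (Safety outcome); latest treatment start 4.5 h after onset (Treatment). Table 2 does not state where the clock starts, so both origins are shown.

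- Clock starts at treatment: (36 − 24) / (36 − 22) = 12/14 = 0.857, or 86% of the window after the limit.
- Clock starts at onset, with treatment at 4.5 h: the limit falls at 4.5 + 24 = 28.5 h, and (36 − 28.5) / 14 = 7.5/14 = 0.536, or 54%.

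These are shares of hours in the window under a strictly literal reading. They are not shares of patients, because the article gives no distribution of scan times. They show only that the two statements do not agree.

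**The case against.** **The article is condensed.** A full seriousness definition, AE forms and DSMC report contents are commonly left to the full protocol, which is not shown. That is fair, and it rules out any claim that such events go unrecorded. It does not rescue the sentence, which is a positive definition and not a gap. If the full protocol defines SAEs properly, the published sentence contradicts it.

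**Exclusions do not forecast events.** They keep higher-risk patients out. This is true, but they do show which harms the protocol associates with the intervention, and those are reasonable ones to watch for in enrolled patients.

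**Stronger readings that the document does not support.**

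- A reader might infer that the safety claim would rest on bleeding and death alone. AE analysis and the day-90 checks are both stated.
- A reader might infer that SUSARs could not be identified, or that contrast reactions would be invisible to the DSMC. All SUSARs are to be reported, without restriction by type. The contents of the DSMC report are not given, so it cannot be said to exclude other events.
- A reader might infer that haemorrhage of any kind counts only up to 24 h, or that 86% of scans are lost. The limit stands in one sentence on haemorrhagic transformation. sICH, which is the labelled safety endpoint and the outcome in the stopping rules, uses the 22–36 h scan. One of its alternative definitions reaches deaths within 7 days, and bleedings reported as SAEs carry no time limit. Table 2 uses 24 h as the nominal name of the 22–36 h visit, so the likeliest explanation is loose wording.

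**Conclusion.** The main point stands. As written, the SAE definition covers two types of event, is narrower than the allergic, cardiac and respiratory risks behind the protocol's own intervention-specific exclusions, and does not fit the SUSAR rule beside it. The consequence is limited but real: serious, non-fatal, non-bleeding events have no stated prompt route to the working group or, through it, to the DSMC. How many patients this affects cannot be derived, because the article gives no rates for such events. The conclusion assumes that sites follow the published sentence and that no fuller definition overrides it.

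The timing point is a minor inconsistency. It concerns haemorrhagic transformation only and leaves sICH and the stopping rules untouched. The 86% and 54% figures measure the mismatch between two phrases, not lost data.

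**What to change.** 1. In Safety monitoring, replace the clause equating SAEs with bleedings and deaths by the full seriousness definition, worded so that bleedings and deaths are included as examples.
2. Tabulate all SAEs by arm, separately for the thrombolysis patients (A and B) and NOR-SASS C, in the remaining 40-patient DSMC reports.
3. Reconcile Safety outcome, Assessment methods, Study endpoints and the abstract on one late scan. Tie haemorrhagic transformation, late recanalisation and lesion volume to the 22–36 h scan and state whether the clock starts at onset or at treatment. The 60-min and optional 2 h recanalisation assessments are not affected.

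**Cost.** The changes of wording are small and alter no treatment rule. There is more SAE paperwork for the sites and a wider DSMC table. The article reports 176 patients enrolled by January 2014 against a target of 276 (176/276 = 64%). Complete by-arm tables may therefore need retrospective collection. Where that is not feasible, the reports should say from which date the wider definition applies.

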### Statistical analysis

Statistical design is made in co-operation with the Centre for Clinical Research, Haukeland University Hospital. An interim analysis will be performed in Q2 2015. The exact method of the final analysis will be specified in the Statistical Analysis Plan, which will be drawn up prior to the closure of the database and the statistical analysis. The primary analysis is an “intention to treat” analysis. The results will also be tested in a “per protocol” analysis. Stratification according to age (≤80 versus >80), baseline NIHSS (≤14 versus >14), time (0–3 h vs. 3-4½ h), occlusion/no occlusion; correct/incorrect insonation focus (patients with no visible occlusion on CTA); atrial fibrillation/no atrial fibrillation will be performed. An analysis excluding MCA_1_ occlusion and MCA_1_- MCA_2_ occlusions will also be performed. Temporal bone window thickness will be included in the analysis. Serious Adverse Events (SAE) and Adverse Events (AE) will be analysed as appropriate.

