### Study endpoints

Primary study endpoints are 1) neurological improvement (NIHSS score) at 24 h (clinical effect; proof of concept) and 2) functional handicap defined as modified Rankin Scale (mRS) score 0–1 at 90 days (clinical outcome). Secondary study endpoints are 1) haemorrhagic transformation (haemorrhagic infarct/haematoma), 2) symptomatic cerebral haemorrhage (safety endpoint), 3) recanalisation at 2 h (optional), 4) recanalisation at 24–36 h, 5) MR-DWI lesion volume at 24–36 h and 6) death.

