### Brain tissue outcome (infarction)

Tissue damage is assessed by 24-h MRI diffusion weighted imaging (DWI) or (CT when MRI is not possible) by a neurologist and/or neuroradiologist blinded to all clinical data, using ASPECTS scoring system [49, 55]. In patients without a visible occlusion on initial CTA the MRI localisation of the lesion is compared with the clinically suspected localisation and will confirm whether the initial ultrasound was aimed at the correct region of interest or not.

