### Delivery of ultrasound to the vasculature

Any stroke trial treatment should ideally be given with a defined dose. Transcranial ultrasound is attenuated through the skull and this reduces the effect of ultrasound. The attenuation varies between patients and the “dose” of ultrasound applied in sonothrombolysis is therefore not standardised. NOR-SASS is a clinical pragmatic study and does not include acoustic measurements to assess the effect of attenuation. Measurements of skull thickness in the area of insonation may, however, serve as a surrogate marker for skull penetration and thereby also the dose of ultrasound applied. In patients without a visualised clot, the investigator judges the clinical picture in cooperation with the treating physician and decides where she/he thinks the probable lesion/clot/ischemia may be. Ultrasound is applied based on this assumption. MR examination the next day demonstrates the DWI lesion(s). The final analysis thereby can include whether or not the initial ultrasound was aimed at the correct region of interest or not.

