## Conclusion

Experimental and human literature supports the view that contrast enhanced sonothrombolysis and contrast enhanced sonolysis improves recanalisation and reperfusion, that it may save tissue at risk, without posing a threat to the patient’s well-being. If a positive effect and safety can be proven by NOR-SASS, contrast enhanced ultrasound treatment may be a pragmatic option for acute ischaemic stroke patients eligible or not eligible for intravenous thrombolysis, for patients with or without a defined arterial occlusion on CTA and for those who do not have access to intra-arterial treatment. And all evidence points in the same direction: sonothrombolysis and sonolysis represent the next step in non-invasive treatment of acute ischaemic stroke.

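### Insonation focus, planned as a stratifier of the treatment effect, is read from the next-day DWI lesion, so comparisons within its strata are not protected by randomisation and can be biased

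*Protocol article*

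**What the plan says.** The Statistical analysis section lists six stratifications that are to be carried out. Five use age, baseline NIHSS, time from onset, occlusion status and atrial fibrillation. The sixth is "correct/incorrect insonation focus (patients with no visible occlusion on CTA".

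Two other sections say how that sixth factor is obtained. Under Brain tissue outcome (infarction), for patients without a visible occlusion, "the MRI localisation of the lesion is compared with the clinically suspected localisation and will confirm whether the initial ultrasound was aimed" at the right region. Delivery of ultrasound to the vasculature adds that "MR examination the next day demonstrates the DWI lesion(s", and that the final analysis can therefore take account of whether the aim was right. Under Assessment methods, the imaging "is performed after 22–36 h to verify the infarct".

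The same scan is an outcome. The Study endpoints section includes "MR-DWI lesion volume at 24–36 h" among the secondary endpoints, and the tissue section states that "Tissue damage is assessed by 24-h MRI diffusion weighted imaging (DWI" (or by CT where MRI is not possible).

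**The concern.** Age, NIHSS, time window, occlusion status and atrial fibrillation are patient or pre-treatment characteristics, so within their strata the arms remain randomised groups. Insonation focus does not have that property. It is known only after the 60 minutes of real or sham insonation, from an image that the treatment is meant to improve. The article's Conclusion says the treatment "improves recanalisation and reperfusion, that it may save tissue at risk". On that premise, some well-aimed active patients may have no lesion the next day. A patient without a lesion cannot be confirmed as correctly aimed, so such patients drop out of the correct-focus stratum in the active arm only.

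What is at stake is how a supporting analysis is read. It asks whether ultrasound works better when aimed at the right place, in patients without a visible occlusion. This is the population that the Discussion presents as new. A biased answer could make well-aimed treatment look less effective than it is.

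**Working it through.** The article states no figure for this analysis, so there is none to reproduce. The check has two parts.

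**Timing.** The aim is chosen when ultrasound is applied. Insonation lasts 60 min. The scan that labels the aim correct or incorrect is made at 22–36 h. The label is therefore post-randomisation and shares its source with an endpoint. This part needs no assumption.

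**Size.** All inputs below are assumed; none comes from the documents.

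*Scenario 1.* 70% of patients are truly well aimed. No DWI lesion is seen in 25% under sham or badly aimed ultrasound, and in 35% under well-aimed ultrasound. A good outcome occurs in 95% without a lesion and 50% with one.

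- Truth in well-aimed patients: sham 0.25×0.95 + 0.75×0.50 = 0.6125; active 0.35×0.95 + 0.65×0.50 = 0.6575. Effect +4.5 points.
- Share labelled correct: sham 0.70×0.75 = 52.5%; active 0.70×0.65 = 45.5%.
- Correct-focus stratum: 50% against 50%. Effect 0.
- Incorrect stratum, lesion-negative patients counted in it: sham (0.25×0.95 + 0.225×0.50)/0.475 = 73.7%; active (0.32×0.95 + 0.225×0.50)/0.545 = 76.4%. Effect +2.7 points.
- Incorrect stratum, lesion-negative patients dropped: 50% against 50%. Effect 0.

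*Scenario 2.* As scenario 1, but well-aimed treatment also raises good outcome from 50% to 55% in patients who still have a lesion.

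- Truth in well-aimed patients: active 0.35×0.95 + 0.65×0.55 = 0.690. Effect 0.690 − 0.6125 = +7.75 points.
- Correct-focus stratum: 55% against 50%. Effect +5.0, so the effect is attenuated.

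*Scenario 3, with differing prognosis.* Half the patients have good prognosis (good outcome 0.7, lesion visible 0.5) and half poor (0.3 and 0.95). The aim is correct in 60%. Well-aimed active treatment abolishes a visible lesion with probability a in good-prognosis and a/2 in poor-prognosis patients.

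- Correct-focus stratum, sham: (0.25×0.7 + 0.475×0.3)/0.725 = 0.438; share 0.6×0.725 = 43.5%.
- With a = 0.4, active: (0.15×0.7 + 0.38×0.3)/0.53 = 0.413; share 0.6×0.53 = 31.8%. Difference −2.5 points. This is what the stratum shows whether abolishing a lesion brings no benefit or a gain of 30 points, because patients whose lesion is abolished are no longer in it.
- With a 30-point gain for each abolished lesion, the true well-aimed effect is 0.25×0.4×0.3 + 0.475×0.2×0.3 = 0.0585, about +5.8 points.
- Over a = 0.1 to 0.4, the true effect runs from about +1.5 to +5.8 points and the correct-focus stratum shows −0.5 to −2.5. If lesion-negative patients count as incorrect, that stratum shows +1.3 to +4.4, although its true effect is 0.
- With a = 0, every difference is 0: no bias.

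*Direction.* Swap the two abolition probabilities at a = 0.4 (0.2 in good-prognosis, 0.4 in poor-prognosis patients). The active correct-focus stratum becomes (0.25×0.8×0.7 + 0.475×0.6×0.3)/(0.20 + 0.285) = 0.2255/0.485 = 0.465, against 0.438 under sham. The selection difference is now +2.7 points. The sign therefore depends on whose lesions disappear.

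**The case against.** Several points on the other side have force.

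- **Location is not volume.** The label rests on where the lesion lies, whereas the endpoint is its volume. A lesion that shrinks but stays visible usually keeps its region and so its stratum. The main route to bias is complete disappearance, which is narrower than any treatment benefit. This stands.
- **The size is assumed.** The zero in scenario 1 follows from giving no benefit to patients with a residual lesion; scenario 2 shows attenuation instead. Benefit moves into the incorrect stratum only if lesion-negative patients are counted there. This stands.
- **It is secondary.** The primary analysis is by intention to treat, and this is one of six listed stratifications. The 90% without visible occlusion, in the Discussion, derives from a local registry and is not the enrolled share. This stands and limits the importance.
- **The analysis plan will settle it.** The article leaves the exact method to that plan, and the section on ultrasound delivery says only that the analysis can include correctness of aim. How lesion-negative patients and stroke mimics are classified is indeed a matter for that plan, and its absence here is no fault. But the article itself commits to the stratifier and defines it from the later scan. That choice is stated, so the objection does not remove the point.

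A reader might infer that the strata are certain to be distorted, or that the analysis will reverse the conclusion about well-aimed ultrasound. The documents support neither: both need treatment to abolish lesions at rates that they do not give.

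**Conclusion.** The point holds in a conditional form. The plan lists, on a par with baseline factors, a stratifier that is fixed after randomisation by a scan that is also a study outcome. That much is certain from the text. Comparisons of the arms within its strata are therefore not protected by randomisation.

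Whether they are biased depends on whether treatment changes lesion visibility, which the protocol's own premise allows. The typical result is a diluted effect in the correct-focus stratum: 0 for a true +4.5, or +5.0 for a true +7.75, in the first two assumed scenarios. Other assumptions give a small negative or positive distortion, or none. The size and direction cannot be settled from the documents. This is a weakness of one supporting analysis that should be corrected, and it is no threat to the primary result.

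**What to change.** In the analysis plan, before any results by arm are seen:

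- Do not present insonation focus as a stratified treatment-effect analysis beside the baseline factors.
- Report agreement between the intended target and the DWI lesion descriptively by arm, with no DWI lesion as its own category.
- Base any stratified effect on pre-treatment data only. Quality of the insonation window at baseline TCCS qualifies, since that examination is done in both arms. The intended target region qualifies only if it is recorded before allocation; the article does not say that it is, so this should be confirmed or the factor left out.
- If the team wants an effect estimate for correctly aimed patients, a principal-stratum analysis with its assumptions stated is an alternative.

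The cost is mainly wording. The loss is real but modest: the comparison by correctness of aim becomes descriptive, and window quality and target region do not fully replace it.
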